### 6.2. Intervention

A single application will be performed for only 30 minutes on each patient.

The area chosen for application will not expose parts of the body and will be easy to apply. To standardize the application, anatomical points will be used as a reference. The location of the placement of the self-adhesive electrodes (5 cm) will be shown in Figure 2. The upper points (electrodes A and B) are three fingers above the spinous process of C7, while the lower points (electrodes C and D) are above the spine of the scapula, above the tender point corresponding to the trapezius muscle.

TENS equipment (Ibramed, Model Neurodyn III, Amethyst Line, two channels) will be used during the study.

The parameters of application of TENS can be adjusted in several ways, but studies have already shown that patients tend to show sensitivity accommodation with a continuous stimulus. Studies that evaluated the decrease in pain compared to control groups obtained better results using the TENS modality with variable intensity and frequency (VIF). These results suggest that it is important to adjust the pulse amplitude during the application of TENS to obtain maximum and longer-lasting analgesic effects when compared to fixed parameter modalities [33, 34].

Regarding the intensity adjustment, a study that evaluated dose response in relation to pain showed that stronger intensities had greater effect. For this reason, it is suggested that the intensity of TENS be applied at the highest possible intensity to obtain maximum pain relief [35].

For the application of the TENS current, the programming is stipulated as described in Table 2.

## 7. Study Procedures (Day 1)

All procedures will be performed within the premises of Pesquisare Saúde (Santo André, Brazil), in the space already equipped and suitable for carrying out international clinical research, and the analysis of blood will be made by the Clinical Analysis Laboratory of the Centro Universitário FMABC (Brazil).

On the day of treatment (D1), after signing the informed consent form (ICF), women will complete an evaluation questionnaire with sociodemographic information, medical history, behavioral habit history, and history of breast cancer (e.g., breast cancer diagnosis, symptoms, staging, and indication for chemotherapy). The questionnaire is described in Supplementary Material 2.

### 7.1. Clinical Laboratory Measurements

The blood will be collected and sent to the clinical laboratory. The study's dependent variables will be the proinflammatory cytokines interleukin 7 (IL-7), interleukin 6 (IL-6), interleukin 2 (IL-2), interleukin 1 (IL-1b and IL-1*α*), and TNF alpha (TNF-*α*) and the anti-inflammatory cytokines interleukin 4 (IL-4), interleukin 4 (IL-10), interleukin 13 (IL-13), and transforming growth factor *β* (FTC*β*).

### 7.2. Data Collection and Analysis Methods

The electrodes for applying TENS will be positioned as described previously (Figure 2). After placement, the patient will be accommodated in an armchair where she will remain until the end of the intervention. 8 ml of blood divided into 4 tubes (2 purple tubes of EDTA and 2 yellow tubes of biochemistry) will be collected by peripheral puncture, in the patient's chosen arm. The tubes will be identified as precollection. In order to make the process less invasive, the patient will have venous access until the end of the second collection.

After the end of the 30 minutes of TENS, the same collection process described above will be repeated. The vials will be identified as postcollection.

Blood collection will take place where the TENS intervention will be carried out (Pesquisare Saúde, Santo André). After collection, the samples will be sent on the same day, at room temperature, to the Clinical Analysis Laboratory of the Centro Universitário FMABC (Santo André, Brazil).

Quantitative analysis of serum levels of proinflammatory cytokines will be performed using the enzyme-linked immunosorbent assay (ELISA) technique (BD OptEIA, Biosciences), following the manufacturer's guidelines and adopting the instructions in the manual as a reference value.

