## 3. Study Objectives and Study Design

A protocol of clinical trials was developed following the guidelines of Standard Protocol Items: Recommendations for Interventional Trials (SPIRIT) [32]. The checklist for SPIRIT can be seen in Supplementary Material 1.

The objective of this study is carried out to assess the reduction of proinflammatory cytokines after TENS application in patients with breast cancer. A nonrandomized, open, single-arm clinical trial with paired analysis will be developed. The study design is described in Figure 1.

A minimum of 59 patients is expected. All subjects will receive a single application of TENS for 30 minutes. Assessments will be made before and after application. Screening data will be reviewed to determine subject eligibility. Individuals who meet all of the inclusion criteria and none of the exclusion criteria will be included in the study. The total duration of the subject's participation will be one day (time to complete all study evaluations).

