## 4. Criteria for Evaluation

The endpoints for the study are described below:

*Primary Endpoint*. The primary endpoint is to analyze the reduction in blood concentration of proinflammatory cytokines.

*Secondary Endpoint*. The secondary endpoints are to analyze the effect size according to each type of proinflammatory cytokine, describe the effect size of the reduction according to breast cancer immunohistochemistry, and analyze the effect on anti-inflammatory cytokines.

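### Section 7.2 does not make the two blood draws comparable: no rest time is fixed before the pre sample and the route of the post sample is unclear, so a modest dilution could be read as a TENS effect

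*Protocol article*

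**What the plan says.** The design is stated in Section 3: "A nonrandomized, open, single-arm clinical trial with paired analysis will be developed". Section 4 sets the outcome: "The primary endpoint is to analyze the reduction in blood concentration of proinflammatory cytokines".

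Section 7.2 gives the sampling sequence.

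- The electrodes are placed and the patient is seated: "After placement, the patient will be accommodated in an armchair where she will remain until the end of the intervention".
- The pre sample is then described as "8 ml of blood divided into 4 tubes (2 purple tubes of EDTA and 2 yellow tubes of biochemistry"), and it "will be collected by peripheral puncture, in the patient's chosen arm".
- To spare the patient, "the patient will have venous access until the end of the second collection".
- For the post sample, "After the end of the 30 minutes of TENS, the same collection process described above will be repeated".

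The cytokine ELISA is described as a measurement in serum. Section 7.2 gives no duration for the time in the chair before the pre draw. Neither it nor Section 8.2 describes a marker of dilution or a correction for it.

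**The concern.** In a single-arm pre/post comparison with no comparator, equal conditions at the two draws are the endpoint's main protection against a measurement artefact. Here the conditions differ in a fixed order. The pre sample follows an unspecified and possibly very short time seated. The post sample always follows that time plus at least 30 minutes.

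If plasma volume rises over that interval, every analyte is diluted, whatever the cytokine-producing cells are doing. The endpoint is a fall in concentration, so such a dilution counts as success. It is systematic, so recruiting more patients makes it more likely to reach significance.

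The route matters for a related reason. If the post tubes are filled from access that has been kept open, any fluid used to keep it open could enter them. If they come from a new puncture, it could not. The text allows either reading.

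**Working it through.** **The plan's own figure.** Section 8.1 gives 59 participants from a 5% probability and a 95% confidence level. The pilot-study formula is n = ln(1 − 0.95) / ln(1 − 0.05) = 58.40, rounded up to 59. The figure reproduces and this point does not affect it.

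**Inputs from the article:** 59 patients, each measured twice; a 95% confidence level (Section 8.2), taken as a two-sided 5% test; 8 ml in 4 tubes, or 8/4 = 2 ml per tube if evenly split.

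**Inputs assumed, because the article does not give them:** the dilution d of the post sample relative to the pre sample (2% to 15%), and the SD s of the within-patient change in log concentration (0.1 to 0.5).

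**Formula.** With no true change in cytokines, the mean log change is ln(1 − d). The standardised paired shift is dz = −ln(1 − d)/s. The chance of a significant fall is the upper tail of a noncentral t with 58 degrees of freedom and noncentrality dz × √59. With no dilution this chance is 2.5%.

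**Example.** For d = 0.10 and s = 0.3: −ln(0.90) = 0.1054; dz = 0.1054/0.3 = 0.351; noncentrality = 0.351 × 7.681 = 2.70; chance of a significant fall = 76%.

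**Result: chance that dilution alone gives a significant fall, paired t-test, 59 pairs**

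| Dilution | s = 0.1 | s = 0.2 | s = 0.3 | s = 0.5 |
|---|---|---|---|---|
| 2% | 33% | 12% | 7% | 5% |
| 5% | 97% | 49% | 25% | 12% |
| 10% | 100% | 98% | 76% | 36% |
| 15% | 100% | 100% | 98% | 69% |

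An 80% chance needs dz = 0.371. At s = 0.3 that is a fall of 1 − exp(−0.371 × 0.3) = 10.5%.

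**If the test is run as independent groups.** Section 8.2 words the comparison as one between groups, although Section 3 promises a paired analysis. With a between-patient log-SD σ, the normal approximation is Φ(−ln(1 − d)/(σ√(2/59)) − 1.96). For σ = 0.3/0.5/1.0 this gives about 15/8/5% at a 5% dilution and 48/21/8% at a 10% dilution.

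**Line fluid, only if the access is flushed or infused (not stated).** An assumed residual of 0.1 to 0.5 ml is 0.1/8 = 1.25% to 0.5/8 = 6.25% of the whole draw. If it all enters one 2 ml tube, it is 0.1/2 = 5% to 0.5/2 = 25% of that tube. This matters only if that tube is assayed, and the tube order is not given.

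**The case against.** The strongest reply has five parts.

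- **The patient is seated before both draws.** This is correct. A reader might infer that the pre sample is taken with no seated period at all. Section 7.2 does not support that: it seats her first, and only the duration is left open.
- **No flush, lock or infusion is mentioned.** Also correct. Without such fluid, what stays in the line is blood. Discard volume and flushing are commonly left to a full protocol or laboratory manual, so their absence from the article is not a fault in itself. Line dilution stays conditional. The difference in seated time does not depend on it.
- **The retained access may simply mean the same route twice.** That is a natural reading, with the repeated process meaning the same tubes and volume. A second puncture is possible too, and would remove the line question. The wording is therefore ambiguous and not a clear contradiction. It still needs settling.
- **The size rests on assumptions.** It does. A reader might infer that dilution alone would make the trial positive. The table supports this only in part: at a log-SD of 0.5, a 5% dilution is significant in 12% of trials. The direction and size of any plasma-volume shift in a seated patient are not in the article, and a shift the other way would hide a true fall.
- **Anti-inflammatory cytokines are already measured and would reveal a common fall.** This is a useful check but not a decisive one. The Discussion hypothesises systemic inhibition, which could itself produce a genuine broad fall.

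What stands against the objection is that the article does fix the sequence, down to tube type, chair, puncture and timing. That sequence gives the two draws different seated times, with nothing to detect the consequence.

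**Conclusion.** The point holds in a limited form. Section 7.2 leaves the rest before the pre draw unfixed and the route of the post draw ambiguous. With no control arm and raw concentration as the endpoint, a common dilution would be counted as the hypothesised reduction.

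Its importance depends on two quantities that the article does not give. Under the paired test the risk of a false positive is substantial at 10% dilution across the assumed SD range (36% to 100%). It is mixed at 5% (12% to 97%). At 2% it is small once the log-SD is 0.2 or more (12% or less). It is lower if the data are tested as independent groups. These figures assume the same proportional dilution in every patient and no true change.

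The documents do not show that dilution will occur, or that it alone would produce the result. They show that the plan could not recognise it if it did. The sample size is unaffected. Whether a true fall is due to TENS is a separate question, which only a comparator can answer.

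**What to change.** In Section 7.2:

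1. Place the venous access, keep the patient seated for a fixed rest (for example 20–30 minutes), then take the pre sample.
2. State one route for both samples, with the same discard volume and tube order at each draw. The discard also matters for step 3: a count on an EDTA tube describes the serum tubes only if line fluid has been cleared before the first tube.
3. Measure haematocrit (Hct) and haemoglobin (Hb) on the EDTA tubes already drawn at both times. Report plasma-volume-corrected concentrations as a sensitivity analysis. If circulating red-cell mass is constant, the plasma-volume ratio is (Hb pre/Hb post) × (1 − Hct post)/(1 − Hct pre), and the post concentration is multiplied by it.
4. Report the within-sample log ratio of pro- to anti-inflammatory cytokines, in which a common dilution cancels, as supporting description only. It should not act as a veto: a rule that withholds the conclusion when both families fall alike has no margin and would also reject a genuine broad fall.

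The cost is about 20–30 more minutes per patient, a small discarded blood volume and a routine blood count on existing tubes. The log ratio uses data already planned. These steps remove or detect the sampling artefact only and do not replace a control arm.

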### 6.1. Blinding

Since it is a sensory current, patients will be blinded regarding the modulation of the current (TENS programming values), but not for the sensation and intensity that must be perceived during the application. All of the patients will be asked about the tingling perception that the current causes, and the intensity limit will be the maximum sensation that is tolerated.

The laboratory technicians will be blinded about the study design and will receive the samples identified by number and the indication of pre and post.

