## 8. Statistical Methods

### 8.1. Sample Size

The sample size was based on the calculation of the sample size in pilot studies proposed by Viechtbauer et al. [36]: 5% probability with 95% confidence level resulted in a sample requiring 59 participants.

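### Section 7.2 sets room-temperature, same-day transport but no equal draw-to-separation time for pre and post tubes; if both are processed together, tube age is confounded with the TENS effect

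*Protocol article*

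**What the plan says.** Section 3 of the protocol article describes the design: "A nonrandomized, open, single-arm clinical trial with paired analysis will be developed". Section 4 makes the within-patient change the main result: "The primary endpoint is to analyze the reduction in blood concentration of proinflammatory cytokines".

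Section 7.2 gives the order of events. Pre tubes are drawn at the research site before stimulation. Then "After the end of the 30 minutes of TENS, the same collection process described above will be repeated". Once both draws have been described, a single handling rule follows, to apply after collection: "the samples will be sent on the same day, at room temperature, to the Clinical Analysis Laboratory". The laboratory belongs to a different institution in the same city.

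The ELISA is to be run "following the manufacturer's guidelines and adopting the instructions in the manual as a reference value". The article does not say when or where tubes are spun, whether the pre tubes leave before the post tubes are drawn, or whether the two sets are separated at the same clock time or at the same elapsed time after their own draws. Under section 6.1 the technicians "will receive the samples identified by number and the indication of pre and post".

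**The concern.** The primary endpoint is the difference between two blood samples from the same woman. Anything that treats the two samples differently in every patient becomes part of that difference. Pairing does not remove it and a larger sample does not average it away.

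Time in the tube before separation could be such a factor. If both sets wait for the second draw and are then processed at one time, the pre sample has stood at room temperature for at least 30 minutes longer. Release of cytokine into the tube would raise the pre value relative to the post value and look like a reduction after TENS. Breakdown would lower the pre value and hide a real reduction. A control group handled in the same way would show the artefact, but this trial has none. Section 10 also says that the results will be used to calculate sample sizes for later trials, so an artefact would carry forward into them.

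**Working it through.** **The plan's own figure.** Section 8.1 reports that "5% probability with 95% confidence level resulted in a sample requiring 59 participants". The number reproduces: n = ln(1 − 0.95) / ln(1 − 0.05) = 58.40, rounded up to 59. The handling issue does not depend on this calculation; 59 is used below only as the number of pairs.

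**Bias from unequal tube age.** Let a(pre) and a(post) be the hours from draw to separation, and r the in-tube drift per hour on the log scale, assumed constant. Then

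measured log change (post − pre) = true log change − r × [a(pre) − a(post)].

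Only the gap between the two ages matters. The total delay cancels within the pair.

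| Processing rule | Age of pre tube (min) | Age of post tube (min) | Gap (min) |
|---|---|---|---|
| One clock time, early | 60 | 30 | 30 |
| One clock time, later | 120 | 90 | 30 |
| One clock time, late | 240 | 210 | 30 |
| Same interval from each draw | 60 | 60 | 0 |

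The ages are examples. The 30-minute gap is the minimum set by the length of the intervention.

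**What the gap could do to the test.** The document gives no drift rate and no SD, so both are assumed. Drift of 5%, 10% and 20% per hour over half an hour gives shifts of about 0.025, 0.05 and 0.10 on the log scale. Drift of 1% and 2% per hour gives 0.005 and 0.01. With no TENS effect, a paired t-test on 59 pairs (58 degrees of freedom, two-sided 5%, critical value 2.002) has noncentrality (shift / SD) × √59, with √59 = 7.681. For a shift of 0.05 and an SD of 0.2, this is 0.25 × 7.681 = 1.92, and the probability of significance in the drift direction is 0.471.

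Probability of significance in the drift direction when TENS has no effect:

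| Log shift over 30 min | SD 0.2 | SD 0.3 | SD 0.5 | SD 0.8 |
|---|---|---|---|---|
| 0 | 2.5% | 2.5% | 2.5% | 2.5% |
| 0.005 | 4% | 3% | 3% | 3% |
| 0.01 | 6% | 4% | 4% | 3% |
| 0.025 | 15% | 9% | 6% | 4% |
| 0.05 | 47% | 24% | 11% | 7% |
| 0.10 | 97% | 71% | 33% | 15% |

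The result depends on the ratio of shift to SD. It runs from negligible to decisive across values that the document does not narrow.

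**The case against.** A reader might infer from section 7.2 that the pre and post tubes always travel together, that every pre tube is at least 30 minutes older when processed, and that tube age is therefore fully confounded with TENS. The text does not say so. What it fixes is an interval of at least 30 minutes between draws. Separate dispatch, separation at the site, or a fixed interval from each draw would all fit the wording, and each could bring the gap to zero. The confounding is therefore conditional. Nor is the delay without limit: same-day is a loose bound, but it is one, and under constant drift the total delay adds nothing to the within-pair bias.

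It can also be said that clotting, spinning and freezing belong in a laboratory manual, that section 9 says collections follow the technical protocols of the services involved, and that the assay follows the manufacturer. This has weight, and an article that was merely silent on bench procedure would give no ground for comment. Here, however, the article does state a handling rule, and the rule as stated does not equalise the two samples whose difference is the endpoint. The reference in section 9 is general and does not show that tube ages are matched. The manufacturer's guidelines are cited for the assay, not for transport.

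The objection to the size also stands. The drift, its sign and the SD are all assumptions, and applying one drift rate to every cytokine is a simplification. The highest percentages come from the combination of large drift and small SD.

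**Conclusion.** The point holds in conditional form. Section 7.2 fixes room-temperature, same-day transport without an equal draw-to-separation time for pre and post tubes. On its most natural reading, with both sets sent after the session and processed together, each pre tube is at least 30 minutes older than its pair. The resulting shift has the same cause in every patient and cannot be separated from a TENS effect in this design.

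The document does not show that a material bias will occur, or in which direction. Under assumed shifts of 2.5% to 10%, the chance of a significant result in the drift direction with no TENS effect is about 15% to 97% at an SD of 0.2 and about 6% to 33% at an SD of 0.5. With drift of only 1% to 2% per hour it is about 3% to 6% over the SDs examined, against 2.5% without drift. These figures rest on constant drift, a gap of exactly 30 minutes and a paired t-test on log values. The case for acting is that the exposure falls directly on the primary endpoint and is cheap to remove.

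**What to change.** In section 7.2, state one draw-to-separation interval and apply it to each tube from its own draw time, so that pre and post tubes are spun separately at the same elapsed time. Leave the length of the interval to the laboratory; what matters for the comparison is that it is the same for both members of a pair. Record the draw and separation clock times for every tube, so that any remaining gap can be described.

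The cost is two timed spins per patient, at the site or at the laboratory, and a time log. No extra blood or patients are needed. If the services already work this way, one sentence in section 7.2 saying so closes the point.

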## 8. Statistical Methods

### 8.1. Sample Size

The sample size was based on the calculation of the sample size in pilot studies proposed by Viechtbauer et al. [36]: 5% probability with 95% confidence level resulted in a sample requiring 59 participants.

### 8.2. Statistical Analysis

For the characterization of the sample, a descriptive analysis of the data will be performed; therefore, the qualitative variables will be described by absolute and relative frequency; the quantitative variables that present normal distribution according to the Shapiro-Wilk test (*p* ≥ 0.05) will be presented as means, standard deviations, and 95% confidence intervals, while those that do not present normal distribution according to the Shapiro-Wilk test (*p* < 0.05) will be presented as medians and respective 95% confidence intervals and 25th and 75% percentiles.

To analyze the quantitative variables between the groups, Student's *t*-test will be used for variables that have a normal distribution and the Mann-Whitney test will be used for variables that do not have a normal distribution.

The confidence level adopted for all analyses will be 95%. All analyses will be performed using the Data Analysis and Statistical Software for Professionals (Stata) version 11.0®.

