## 6. Study Intervention

The consent form will be obtained as the first procedure from all participants by the study coordinator. The confidentiality of the data will be guaranteed until the end of the research.

The study will not be randomized. All patients will be submitted to TENS intervention, and the data will be analyzed in the pre- and postintervention of each patient.

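### Section 8.2 lets a normality verdict choose between two independent-samples comparisons in a paired pre/post trial; one prespecified paired analysis for every cytokine should replace it

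*Protocol article*

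**What the plan says.** Section 8.2 opens with sample description. There, "the quantitative variables that present normal distribution according to the Shapiro-Wilk test" at p ≥ 0.05 are summarised by mean, SD and 95% CI, and the others by median, 95% CI and quartiles. The next paragraph covers inference and begins: "To analyze the quantitative variables between the groups, Student's". It assigns the t-test to variables judged normal and Mann-Whitney to all others. Shapiro-Wilk is the only normality criterion in the article. The section sets 95% confidence throughout.

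The design is stated elsewhere. Section 3: "A nonrandomized, open, single-arm clinical trial with paired analysis will be developed". Section 6: "the data will be analyzed in the pre- and postintervention of each patient". Section 4: "The primary endpoint is to analyze the reduction in blood concentration of proinflammatory cytokines", with a secondary endpoint to "analyze the effect size according to each type of proinflammatory cytokine". Section 7.1 names the cytokine measurements themselves, not their changes, as the dependent variables.

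**The concern.** Three things do not fit together.

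- **Tests and design.** Mann-Whitney is a test for independent samples, and a t-test between groups reads the same way. The data are two measurements on the same woman, so the valid comparison rests on the within-patient change.
- **The switch.** A paired analysis depends on the distribution of the change. Section 8.2 does not mention the change. On the natural reading of Section 7.1, the screen is run on the concentrations. Each cytokine then has two verdicts, pre and post, and nothing says what happens when they differ. The test for the primary endpoint is then an open choice made with the data in hand.
- **Comparability.** If some cytokines are reported as means with a t-test and others as medians with a rank test, the per-cytokine effect sizes promised in Section 4 do not share a scale. Section 10 also plans to size later trials from these results. That needs the variability of the within-patient change, which the stated summaries do not provide.

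**Working it through.** **The plan's own figure.** Section 8.1 derives 59 from 5% probability and 95% confidence: n = ln(1 − 0.95)/ln(1 − 0.05) = 58.40, rounded up to 59. It reproduces. It is not a power calculation, so this point does not change it.

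**Inputs.** From the article: 59 pairs, Shapiro-Wilk cut at 0.05, 95% confidence. Assumed, because the article gives none of them: two-sided α of 0.05, lognormal concentrations, pre/post correlation ρ = 0.8 on the log scale, log SD s from 0.2 to 1.0. The effect is 0.371 SD of the log change. This gives noncentrality 0.371 × √59 = 2.85 and 80% power for the paired t-test on log(post/pre).

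**1. How often is the rule undefined?** Simulated share of cytokines where Shapiro-Wilk passes one time point and fails the other:

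| Log SD | Pre and post disagree |
|---|---|
| 0.2–0.3 | about 31–32% |
| 0.4 | 18% |
| 0.5 | 7% |
| 0.8–1.0 | about 0% |

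With correlation varied from 0.5 to 0.9, the range is 24–44% at log SD 0.2–0.3 and 5–9% at 0.5. Section 7.1 lists six proinflammatory analytes. If they were independent, the chance of at least one disagreement would be 1 − 0.69⁶ = 89% at a rate of 31%, 1 − 0.82⁶ = 70% at 18% and 1 − 0.93⁶ = 35% at 7%. Independence is doubtful for cytokines from the same blood sample, so these three figures are only indicative.

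**2. What do the unpaired tests cost?** On the log scale the true standard error of the mean difference is s√(2(1 − ρ)/n), whereas an unpaired test uses s√(2/n). The ratio is √(1 − ρ) = √0.2 = 0.447. The unpaired statistic therefore has mean about 2.85 × 0.447 = 1.27 and SD about 0.447, against a critical value of 1.98. Power is about P(Z > (1.98 − 1.27)/0.447) = P(Z > 1.58), or about 6%. Simulating the written rule on raw concentrations (unpaired t if both time points pass, otherwise Mann-Whitney) gives about 7–9%, against 80% for the paired log-ratio t-test. With no true change, the written rule rejects in 0–0.8% of trials instead of 5%. The error is towards missed effects, not false positives.

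**3. What does the switch cost if the tests are paired?** Same setting, same screen on the concentrations, paired t or Wilcoxon signed-rank, with the rank test when the time points disagree:

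- log SD 0.2 and 0.3: 79% against 81%, and 77% against 79%, for the log-ratio t-test;
- log SD 0.5, 0.8 and 1.0: 74%, 72% and 71%, against 80–81%.

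The loss is about 2–10 points. Moving the screen from the concentrations to the change alters power by about 1 point or less.

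**4. Other settings (power).**

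| Setting | Written rule | Same switch, paired tests | Log-ratio t |
|---|---|---|---|
| Lognormal, ratio 0.8, log SD 0.5, ρ 0.5 | 70% | 88% | 92% |
| Lognormal, ratio 0.8, log SD 0.8, ρ 0.8 | 17% | 86% | 92% |
| Additive normal, CV 0.30, ρ 0.5, 10% fall | 41% | 71% | 64% |

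Pairing gives the large gain in every row. The log scale helps in the first two and costs 7 points in the third.

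**The case against.** **The Shapiro-Wilk sentence concerns description, and raw-value screening is inferred.** Both are true. The sentence introduces the characterisation of the sample, and Section 8.2 speaks only of quantitative variables. But the next paragraph makes the test depend on normality, no other criterion is given, and Section 7.1 names the measurements as the dependent variables. The inference is reasonable and should be stated as one.

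**Section 3 already promises a paired analysis, and Student's t-test has a paired form.** This may well be the intention. It does not rescue Mann-Whitney, which has no paired form. If the groups meant are patient subgroups instead, Section 8.2 names no test for the pre/post comparison.

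**Transformations and tie-breaks belong in an SAP.** Their absence alone would be no finding. The point is that the article does state a rule, and that rule conflicts with the design.

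**Stronger readings that the documents do not support.** A reader might infer that screening the concentrations is what costs the power; that accounts for about 1 point or less. A reader might infer that power falls to 49–60%, which is what a paired t-test on raw values gives at log SD 0.8–1.0. At that skew both time points almost always fail the screen, so the rule would choose the rank test. A reader might infer that the rule is usually undefined, but disagreement vanishes with strong skew. Nor do the documents show that logs are better: they give no distribution, SD, correlation or rate of readings below the assay limit.

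**Effect size is not tied to the Shapiro-Wilk summaries.** Correct: Section 4 leaves it undefined. Mixed summaries therefore hamper the comparison across cytokines but do not rule it out.

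**Conclusion.** The point holds in this form: Section 8.2 chooses by a normality verdict between two comparisons worded for independent groups, while Sections 3, 4 and 6 define a paired trial whose endpoint is a within-patient reduction.

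The mismatch with the pairing is the serious part. It gives about 7–9% power where a paired log-ratio t-test has 80%, at an assumed correlation of 0.8, and the loss is smaller at lower correlation. The switch is a lesser defect. It is undefined for about a third of cytokines under mild skew and almost never under strong skew, and with paired tests it costs about 2–10 points under lognormal data. The preference for logs is conditional, since they could lose up to about 7 points under additive normal data. All power and disagreement figures rest on assumed distributions. The contradiction between test and design does not.

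**What to change.** In Section 8.2, drop the Shapiro-Wilk switch for inference and prespecify one paired analysis on one scale for all cytokines. For example: analyse log(post/pre) with a paired t-test for every cytokine, report the geometric mean ratio with its 95% CI as the effect size, and use the Wilcoxon signed-rank test on log(post/pre) as sensitivity analysis. Remove Mann-Whitney from the pre/post comparison. If it is kept for comparing patient subgroups, say so. Report the SD of the log change for each cytokine, which Section 10 needs for sizing later trials. Shapiro-Wilk may stay for describing baseline characteristics.

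The cost is a few sentences, with no change to the sample size or data collection. The small downsides are that values below the assay limit need a stated substitution rule before logs are taken, and that some efficiency is lost if the data are not right-skewed.
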